### What is the task?

The experiment examines the effect of grammatical-gender on occupational associations through prompted speech production. This is achieved through a speech production task based on an adaptation of the popular board game ’Taboo’ [26]. The participant’s target is to produce as many words as possible related to the prompt to increase their score, without repeating the prompt word itself. Participants are asked to complete this speech production task with a pre-specified time limit, while repeatedly pressing the spacebar, which will act as an attentional load. Working memory and attention is limited [27, 28]. The attentional load in the task can affect the participant’s speech in various ways [29, 30]. In this experiment, the purpose of the attentional load is to reduce speech planning capabilities, thereby increasing reliance on subconscious associations corresponding to implicit beliefs relating to S-gender and occupation.

Participants will be prompted both audibly and visually, where the target word is initially played and visually remains on the screen until the timer runs out. The auditory prompt is to ensure the correct interpretation of the visual target, while avoiding adding diacritics to the visual primes which could result in confounding effects and slower processing for less ‘obvious’ phonetic interpretations [31]. Un-diacretised words presented on their own or out of context can often be ambiguous between several pronunciations. Context is usually sufficient to disambiguate, and therefore outside of pedagogical contexts, fully diacretised text is highly unusual. The visual prompt will be presented on screen for a duration of 20 seconds.

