### Design

The experiment employs both between and within variation and is randomised through a block design (5 blocks). The first factor, which varies between participants, is the language condition. There are four main language conditions, and one sub-condition: singular masculine generics, singular feminine g- gender, gender inclusive binomial word-pairs, English gender neutral, and plural masculine generics as the sub-condition (see Table 1).

**Table 1 pone.0292936.t001:** Between variation and breakdown of conditions.

Condition		Example
**1.**	Singular generic masculine	مدرس ‘Teacher[+masc]’
**1.1**	Plural generic masculine	مدرسين ‘Teachers[+masc]’
**2**	Singular feminine	مدرسة ‘Teacher[+fem]’
**3**	Gender-inclusive: Feminine/Masculine word-pair	مدرسة/ مدرس ‘Teacher[+fem]/Teacher[+masc]’
**4**	Gender-neutral: English neutral	Teacher

There is one factor that varies within-participant and that is the ‘stereotypicality’ of the role. Role nouns can be associated with men (e.g., *manager*), associated with women (e.g., *nurse*), or neutral (e.g., *student*). All participants are presented with the same 12 role nouns (4 in each stereotype) but in different language conditions.

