### Outcomes of interest

To answer the research questions outlined above, the study focuses on two outcome categories: fluency measures and the participant’s gender interpretation of the prime.

Fluency measures consist of 5 dependent variables: the total number of words produced, hesitation markers, number of false starts, fluency mistakes, and initial response time. These measures are consistent with current literature on speech production [34]. The focus on fluency allows for exploration of processing costs and benefits due to in/congruent or asymmetric stimuli. Additionally, fluency measures help show what is easily accessed or recalled. Processing benefits are expected when participants’ S-gender expectations are not violated (i.e., a *secretary* in feminine morphology and a *manager* in masculine morphology compared to a *secretary* in the masculine). Importantly however, roles associated with women presented in masculine morphology should *not* result in processing costs if masculine G-gender is truly interpreted as generic or unmarked.

To measure the participant’s interpretation of the prime their responses will be coded based on the proportion of gendered morphosyntactic markers in their speech. Importantly, this will be weighted at the tensed phrase (TP) level. This is to avoid inflating scores based on morphosyntactic markers for the sake of agreement across noun phrases or verb phrases. This coding will be used to derive two other categorical variables to be used in the analysis: the participant’s gender expectations and whether the expectations are congruent with the social stereotype associated with the prime.

Example 3 provides a fictitious response to the stimulus “*manager [+masc]*” and how this would be coded. Firstly, we can see that there are three morphosyntactic markers that are masculine, two of which are used only for agreement purposes. Secondly, we can determine that the participant interpreted the stimulus to be a man and that this response is congruent with the prime (i.e., grammatical gender and social gender are not asymmetric).

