Similarly, in condition 4 (neutral English), stereotypical information may inform participants’ gender expectations, such that *doctors* are more likely to be men and *secretaries* are more likely to be women in responses. If this is the case, then the fixed effect for language in conditions 3 and 4 should not be statistically different. Importantly, in this condition participants have the option to respond in the gender neutral ‘they’ instead of assuming the role’s gender. Therefore, some variation between feminine, masculine, and neutral pronouns could be expected. If this condition also elicits highly gendered responses based on social stereotypes, then this presents evidence on the importance of gender-fair and representative language rather than just neutral language. This has implications for jobs advertised in English, which are assumed to be gender-neutral in interpretation but may instead entrench participant’s existing stereotypes.

Additionally, it is expected that fluency measures in congruent conditions will exhibit processing benefits (i.e., fewer fluency mistakes, more speech produced within the time limit, less hesitation, and reduced lag time) compared to their incongruent counterparts. Where grammatical information and stereotype information are incongruent (i.e., *nurse* presented in the masculine or *manager* presented in the feminine), it is predicted that outcomes related to fluency and initial response time will be negatively affected and participants will experience processing costs as a result of a violation of expectations. Importantly, interpreting masculine G-gender as generic should not be as costly or inefficient because it can be used to refer to male or female S-genders.

Further, condition 3 should not show significant differences in fluency or response time due to stereotype or number variation. This is because G-gender and stereotype information can always be congruent in a word-pair. Similarly in condition 4, it is predicted that fluency and response time will not vary across stereotype or number.

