It is worth noting that condition 3 (inclusive language) as a whole compared to other conditions may trigger longer response times and processing costs because the word-pair may lead to initial hesitation as to which form of gender agreement the participant should select given that both the masculine and feminine are presented. Additionally, fem/masc combinations are not as frequent as masc/fem combinations and so some order effects/lag time are expected in this condition. This condition may also elicit plural morpho-syntactic markers if participants interpret the word pair as having both one male and one female referent.

Similarly, condition 2 (feminine G-gender) as a whole is likely to show processing costs, as role nouns associated with men or those that are neutral are lower frequency in the feminine compared to their masculine counterparts. That being said, both the feminine and masculine versions of a role noun share identical root morphemes and vary only in suffixes so differences in fluency can directly be attributed to the infrequent use of feminine role nouns. Consequently, the English version of the experiment, and masculine generic conditions in Arabic are expected to trigger higher fluency scores compared to the other conditions.

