## Pre-specified analysis plan

The study uses mixed effects regression, modelled in STATA, to account for within and between variation in the experiment. There are two different outcome categories and therefore multiple models will be used to explore the effect of language on the dependent variables outlined above.

The first set of models related to fluency will utilise linear-mixed-effects models, and models related to gender expectations will use generalised linear mixed effects models for categorical dependent variables. In both cases, the language condition will be defined as the fixed effect. The models will include random slopes for this fixed effect as some occupations may be more affected by the language condition than others. By-participant random slopes and intercepts will be included in the models as random effects. This is because participant variation is expected due to differences in demographic information (age and gender), attitudes towards women (from the exit survey), language dominance measures (exit survey), and participant’s nationality (note that this is likely corelated with attitudes towards women, and highly correlated with language dominance measures). Similarly, by-item random slopes and intercepts will be included as variation due to length of stimuli or familiarity with different occupations should be accounted for.

Interaction effects will be explored between stereotype and language condition, and for a subsample of the data interactions between number and stereotype will also be explored. Interaction effects related to number will help assess the mediating effect of number on gender expectations in masculine grammatical gender.

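### The predicted English advantage in fluency cannot be read from word counts, because an English word and an Arabic word are not the same unit

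*Protocol article*

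**What the plan says.** Under Hypotheses, the protocol article closes its discussion of the feminine and word-pair conditions by predicting that "the English version of the experiment, and masculine generic conditions in Arabic are expected to trigger higher fluency scores" than the remaining conditions. The conditions left over are the Arabic feminine and the Arabic word-pair, so this is a directional claim that English exceeds Arabic.

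Outcomes of interest states that "Fluency measures consist of 5 dependent variables" and lists them as "the total number of words produced, hesitation markers, number of false starts, fluency mistakes, and initial response time". The task description makes the count the participant's goal as well: participants are to "produce as many words as possible related to the prompt to increase their score".

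The Design section puts English in the same between-participant factor as the Arabic conditions; its list ends with "gender inclusive binomial word-pairs, English gender neutral, and plural masculine generics as the sub-condition". The Pre-specified analysis plan assigns linear mixed models to the fluency outcomes and generalised models to gender expectations, and adds: "In both cases, the language condition will be defined as the fixed effect".

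**The concern.** A word count compares fluency between two groups only if a word costs about the same to produce, and carries about the same content, in both. Within Arabic that is a fair working assumption. Across Arabic and English the protocol's own linguistic description speaks against it. If English spreads the same content over more words, the English count rises in the predicted direction without anyone speaking more fluently. The result could then pass as support for the stated prediction.

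The groups also differ in who they are. Half of the English block are British monolinguals, so the contrast is not wholly randomised and mixes language with population.

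**Working it through.** **1. Is the unit the same?** These parts of the protocol article bear on it.

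- *How does Egyptian Arabic do gender?* says that Arabic marks gender and number on pronouns, verbs, nouns and adjectives.
- *Example 3* glosses a three-word Arabic sentence. One word holds the definite article, the stem, gender and number. Another holds third person, progressive aspect, gender and the verb itself.
- *Outcomes of interest* weights by tensed phrase, but only when coding gender markers. No such rescaling is described for fluency.

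The units differ by the protocol's own account, and the article gives no common unit or within-language baseline for word counts.

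**2. Can the model remove the difference?** The plan includes by-participant and by-item random intercepts and slopes. A shift shared by every English trial coincides with the English level of the fixed effect. Random effects vary around that level and cannot take the shift out.

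**3. Does the stated reasoning cover English?** The argument just before the prediction is that feminine role nouns are less frequent than masculine ones but share their roots. That supports masculine against feminine within Arabic. It gives no ground for English against Arabic.

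**4. Who is compared?** From Sample size: 4 × 30 in blocks 1–4, plus 30 bilinguals and 30 monolinguals in English, gives 120 + 60 = 180, which agrees with the stated total. The monolingual share of the English block is 30/60 = 50%.

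**5. How large could the artefact be?** The documents give neither a word ratio nor an SD, so this is an illustration under assumptions.

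- Arabic participants: 3 × 30 = 90 (blocks 1–3, where each person sees all three singular conditions). English: 60.
- Alpha 0.1, as named for the later power analysis; two-sided is assumed.
- True fluency is equal. The Arabic mean is scaled to 1 and the English mean is r, through segmentation alone.
- SD of a participant's mean count, as a fraction s of the mean: 0.3, 0.4 or 0.5.

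SE = s × √(1/90 + 1/60) = s × √(1/36) = s/6.

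P(significant) = Φ((r − 1)/SE − 1.645) + Φ(−(r − 1)/SE − 1.645).

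For r = 1.1 and s = 0.3, SE = 0.05 and (r − 1)/SE = 2.0, so P ≈ Φ(0.355) ≈ 0.64. The others follow in the same way:

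| r | s = 0.3 | s = 0.4 | s = 0.5 |
|---|---|---|---|
| 1.0 | 0.10 | 0.10 | 0.10 |
| 1.1 | 0.64 | 0.44 | 0.33 |
| 1.2 | 0.99 | 0.91 | 0.77 |

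With 30 against 30, r = 1.2 gives 0.83, 0.61 and 0.46.

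The calculation ignores between-item variation in the language effect, which the planned by-item slopes would add to the standard error; that would lower the figures. The bias itself does not shrink with sample size. More participants make a false difference more likely to reach significance, so the power analysis planned after the pilot cannot cure it.

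**The case against.** The strongest case on the other side has four parts.

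*Four of the five measures do not depend on word segmentation.* This stands. Hesitations, false starts, mistakes and response time are not counts of content words. A reader might infer that the English prediction could never fail for a genuine reason, but that goes too far: it can fail on any of these four. The prediction also ranks the Arabic masculine generic high, and that part is untouched. Across languages the four measures still face the language and population differences.

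*The example does not fix a ratio.* This also stands. One could add the article that the gloss marks and get four English words for three Arabic ones, an excess of 33%. The protocol's own free translation has three words for three and omits the article. No figure can be drawn from it, and rules on which words count may sit in a fuller document.

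*A single pooled fluency model is not stated.* The plan speaks of multiple models, and the study is described in three components with English separate. Table 5 gives only within-condition fluency predictions for English. This is fair, but the text still commits to English scoring above the Arabic conditions, and testing that needs a cross-language contrast however the models are split.

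*The protocol admits that culture and language cannot be fully separated.* It does so under Participants' characteristics, for bilinguals against monolinguals in the gender-neutral condition. It does not extend this to word counts across languages.

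Two further readings should be avoided. The statement that "the fixed effect for language in conditions 3 and 4 should not be statistically different" could be taken as a planned cross-language fluency test; its context is gender expectations, and fluency comes up only afterwards. Nor does the protocol say that a higher English count would be reported as a benefit of neutral language.

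**Conclusion.** The concern holds for one secondary prediction and one outcome. The protocol predicts higher fluency in English than in the Arabic feminine and word-pair conditions and includes raw word count among the measures. Its own description shows that the word is not a common unit, so a higher English count cannot be attributed to fluency.

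The size of the artefact is unknown. The range of about 33% to 99% rests entirely on the assumed 10% to 20% excess, the assumed SD of 30% to 50% of the mean, two-sided alpha 0.1 and the 90 against 60 comparison. Even the direction of the net effect is suggested by the gloss rather than established.

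A reader might conclude that the study's main question is compromised. It is not: the contrasts among masculine, feminine, word-pair and plural within Arabic, the stereotype contrast within English, and bilingual against monolingual within English are each made in one language, so this unit problem does not reach them.

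**What to change.** In Hypotheses, remove the English-against-Arabic part of the fluency prediction for word count, or label it descriptive. In the Pre-specified analysis plan, state that word counts will be modelled or contrasted only within a language: masculine, feminine, word-pair and plural within Arabic; stereotype, and bilingual against monolingual, within English. Report any cross-language difference in the other four fluency measures as confounded by language and population.

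A same-language baseline from the animal prompts might look like a ready alternative. The protocol lists only four of them and does not say that responses to them are scored or that they appear in the English block, so this would have to be confirmed first.

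The cost is a change of wording and the loss of one secondary cross-language prediction. Recruitment, stimuli and allocation stay as they are.

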#### Participants’ characteristics

Participants’ age, gender, stereotype beliefs, or level of aversion to women in the workplace will be collected to check for mediating effects on gender expectations and responses to stimuli in the gender-exclusive conditions. Bilingual Egyptian participants and monolingual UK respondents are expected to show differences in the gender-neutral condition. Cultural differences in the perception of women and differences in occupational expectations may affect their responses. Further, bilingual Egyptians might be more likely to interpret English neutral language as masculine due to carryover effects from Arabic as well as a more obvious level of gender segregation in Egypt compared to the UK where some of the gender stereotypes may not be as salient. Crucially, if neutral G-gender primes male occupational expectations for both bilingual and monolingual English speakers, this will show large potential for change through attention to inclusive and gender-fair language in both Arabic and English-speaking contexts. However, if significant differences arise between both types of participants this could help show the influence of either cultural differences (as proxied by the exit survey on aversion to women in the workplace) or linguistic differences and gender carryover effects from Arabic to English. The current design of the experiment is incapable of fully disambiguating these cultural and linguistic factors, but this could point to an important area of future research on bilingual processing to determine if carryover effects are driving this variation or sociocultural differences.

### Sampling & participant recruitment

#### Sample characteristics

There are three types of participants that will be recruited for the study: ‘native’ Egyptian Arabic speakers, monolingual British English speakers, and Egyptian bilinguals with ‘native level’ proficiency in both English and Arabic. Fig 1 presents the possible blocks that different participants can be allocated to depending on their characteristics. For all Arabic blocks, Arabic speakers residing in or who have previously resided in Egypt for at least 10 years will be recruited. All other Arabic-speaking countries will be excluded, this is largely because the norming and stereo-typicality of the stimuli is based on an Egyptian sample and so the ecological validity of these categories has not been tested in other Arabic-speaking settings. However, this is not expected to affect the generalisability of the results as the classifications of these roles are likely to be regionally consistent.

Regardless of language spoken, the study will be targeting a gender-balanced sample of participants aged 18 and above. There will be no restrictions placed on age, but age will be included in the mixed effects model as a potential moderating factor.

#### Participant recruitment & data collection

Both the English-speaking and Arabic-speaking sample will be recruited through online resources (Twitter, Facebook, and Linked-In), university mailing lists, and Prolific (if needed). Data will be collected online (on the participants’ personal device) and in person (in a university lab).

#### Exclusion criteria

Participants not sufficiently proficient in English (for the English Condition) or Arabic (for the Arabic conditions) will be excluded from the analysis. Proficiency will be determined using a C-test, and results below native-level proficiency will be excluded (this corresponds to a score of less than 90% on the test). Additionally, participants that are aware of the purpose of the experiment, based on their responses in the exit survey, will be excluded. Finally, participants that repeatedly or purposely ignore the two key tasks (pressing spacebar and producing speech) for more than 2 occupations will be excluded.

#### Sample size

As this is a novel experiment, an estimation of the effect size based on the previous literature or pilot data is not possible. Consequently, a power analysis cannot be conducted at this stage. As such, the study will initially target the average sample size (30 participants) per condition in the relevant existing literature. Therefore, at present the sample will consist of at least 30 participants in blocks 1–4, and 30 Egyptian bilinguals plus 30 monolinguals in the English block (total of 180). However, after conducting the pilot we will use the results to conduct a formal power analysis in STATA (power 0.9 and *alpha* 0.1) to check if additional participants are required.

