## Piloting

This experiment will be piloted in one round if there are no adjustments necessary based on the piloting. However, if changes are required based on the initial pilot, an additional smaller round of piloting will be conducted, and size will be determined based on the magnitude of the change. For example, if the change only affects block 5, other blocks will not be subject to additional piloting. In the first round, blocks 1–3 will be piloted with 3 participants each, block 4 will be piloted with 4 participants, and block 5 will be piloted with 6 participants (3 Egyptian bilinguals and 3 English monolinguals). Based on the initial pilot, the following changes can be made. Firstly, stimuli will be changed (if necessary) based on the stereotype norming exercise. Secondly, the time allocated to participants to produce speech can be increased or decreased from the initial 20 seconds if this is found to be insufficient or too abundant. If no changes are made based on the pilot, the participants’ observations will be included in the analysis.

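### A power check fed by a 19-person pilot cannot be relied on to secure 0.9 power for small or moderate effects

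*Protocol article*

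**What the plan says.** The Sample size section of the protocol article explains that "an estimation of the effect size based on the previous literature or pilot data is not possible", so no power analysis is done yet. It adopts 30 per condition, the average in related work: at least 30 in each of blocks 1 to 4, plus 30 bilinguals and 30 monolinguals in block 5, 180 in all. It then commits to a later check: "after conducting the pilot we will use the results to conduct a formal power analysis in STATA". The targets of that check are a power of 0.9 and an alpha of 0.1, and its purpose is to show whether recruitment must go beyond 180.

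The Piloting section fixes the size of that pilot: "blocks 1–3 will be piloted with 3 participants each, block 4 will be piloted with 4 participants". For the English block, the pilot takes six people, three from each language group. Neither section names the contrast or outcome to be powered, a smallest effect of interest, the sidedness of the test or a maximum sample size.

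**The concern.** The plan's one formal safeguard on sample size is a calculation whose key input would come from 3 to 9 people per contrast. An effect size estimated from so few is mostly sampling error. A pilot that overstates the effect leaves recruitment at 180 when more people are needed. A pilot that understates it asks for a number nobody can recruit. In either case the report could say that the study was powered at 0.9 when the procedure does not have that property. Null findings on smaller effects, such as the fluency costs or the bilingual carry-over, would then look more conclusive than they are.

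**Working it through.** **The plan's own figure.** 4 × 30 + 30 + 30 = 180, as stated. The 0.9 power cannot be reproduced, because no effect size or standard deviation is given.

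**Pilot size per contrast (Piloting section; Tables 2 to 4).**
- Blocks 1 to 3: 3 × 3 = 9. The Design section calls language a between-participant factor. Under the Table 2 Latin square, though, each participant meets 4 masculine, 4 feminine and 4 word-pair nouns, so these contrasts are within participants: 9 in the pilot, at least 90 in the study.
- Block 4, plural: 4, compared with 9 for the singular.
- Block 5: 3 bilinguals against 3 monolinguals.
- Total: 9 + 4 + 6 = 19.

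**Precision of a pilot effect (noncentral t, 95% interval for an observed 0.5).**
- 3 v 3: −1.16 to 2.11.
- 4 v 9: −0.71 to 1.68.
- 9 within participants: −0.21 to 1.18.

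**Required size.** Two-sided alpha 0.1 (sidedness is assumed) and power 0.9 give z = 1.645 + 1.282 = 2.926.
- Between groups, n per group = 2 × 2.926² / d²: 191 at d = 0.3, 69 at d = 0.5, 27 at d = 0.8.
- Within participants, n = 2.926² / dz²: 381 at dz = 0.15, 215 at dz = 0.2, 96 at dz = 0.3.

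**When the check adds nobody.** It reports 30 per group as enough when the observed |d| is at least 2.926 × √(2/30) = 0.76. It reports 90 as enough when the observed |dz| is at least 2.926 / √90 = 0.31. In both cases this means a pilot t statistic of only about 0.93 (4 df or 8 df).

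**Behaviour of the whole rule.** Size comes from the pilot effect, is never below the minimum, and is capped at 300 per group or 900 within participants. The final analysis is a t test on one value per participant, without the pilot data. The true effects and caps are assumptions.

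| True effect | Size needed | Check says minimum is enough | Power at the minimum | Actual power of the rule |
|---|---|---|---|---|
| d = 0.3 (3 v 3) | 191 per group | 44% | 0.31 | 0.56 |
| d = 0.5 | 69 per group | 48% | 0.61 | 0.77 |
| d = 0.8 | 27 per group | 58% (correctly) | 0.92 | 0.95 |
| dz = 0.15 (9 within) | 381 | 43% | 0.41 | 0.65 |
| dz = 0.2 | 215 | 46% | 0.59 | 0.77 |
| dz = 0.3 | 96 | 54% | 0.88 | 0.93 |

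At d = 0.5 the middle half of the resulting sizes runs from 30 (the floor) to about 150 per group. Raising the between-group cap to 1,000 leaves the three between-group powers unchanged to two decimals. Lowering it to 100 gives 0.47, 0.76 and 0.95.

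**What 180 detects with power 0.9.**
- 30 v 30: d = 0.76 at two-sided alpha 0.1. At 0.05 (z sum 3.242), 3.242 × √(2/30) = 0.84.
- 90 within participants: dz = 0.31 at 0.1. At 0.05, 3.242 / √90 = 0.34.

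**The case against.** The strongest reply is that the pilot can only add participants. The stated minimum holds whatever the pilot shows, and it gives about 0.9 power at alpha 0.1 once d reaches 0.76 between groups or dz reaches 0.31 within. The Hypotheses section expects grammatical gender to override stereotype, which implies a large effect on gender interpretation. This stands, so a reader who infers that the plan can never reach 0.9 power goes too far.

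A second reply is that 3 against 3 describes only the bilingual comparison, the third aim, and not the primary Arabic contrasts. That also stands, and it is why the within-participant case is shown separately. With 9 pilot participants the check still misses often at dz = 0.2.

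A third is that the article says only that pilot results will be used, which does not exclude using them for variance alone. That is possible. But the section gives the absence of an effect size as its reason for deferring the calculation, and it offers no other source for one.

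Two further inferences are not supported:
- **Reuse of pilot data.** A reader might think that it costs power. It is conditional on no changes after the pilot and slightly raises the rejection rate. With the minimum in force, type I error goes from 0.10 to about 0.105.
- **Alpha 0.1 across the outcomes in Table 5.** A reader might infer a large familywise error. The article does not state the level at which outcomes will be tested, independence of the fluency measures is unlikely, and multiplicity is commonly left to an analysis plan that is not shown here. A lenient alpha does not of itself lower power.

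**Conclusion.** The concern holds in limited form. A check at "power 0.9 and *alpha* 0.1" that takes its effect size from this pilot does not secure 0.9 power for small or moderate effects. Actual power is about 0.56 to 0.77 for d of 0.3 to 0.5 and about 0.65 to 0.77 for dz of 0.15 to 0.2. In a little under half of pilots it wrongly reports that the minimum is enough. For large effects (d = 0.8, dz = 0.3) the rule gives 0.95 and 0.93, mainly because of the minimum and not because of the pilot.

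These figures rest on assumed true effects and caps, a two-sided test, one value per participant in place of the crossed mixed model, and the reading that the pilot supplies the effect size. The exact powers would change under the full model. The imprecision of an effect estimated from 3 to 9 people would remain.

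**What to change.** - For each main question, name the contrast and outcome to be powered, and pre-state the smallest effect of interest.
- Use the pilot at most for variance components, with an allowance for their imprecision, such as an upper confidence limit. From 3 v 3 (4 df) the standard deviation is known only to within a factor of 0.60 to 2.87.
- Compute power by simulating the planned crossed participant-by-noun model, at the alpha and sidedness at which that contrast will be tested.
- If recruitment stays at 180, replace the 0.9 target with the detectable effect for each contrast: about d = 0.76 for 30 v 30 and dz = 0.31 for the 90 participants in blocks 1 to 3 at two-sided alpha 0.1 (0.84 and 0.34 at 0.05), updated once the simulation has been run.

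The cost is a few hours of simulation and some rewording before main recruitment. The downside is that the stated power or detectable effect will look less favourable.
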